##### Formative Study for Developing the Health Promotion Module (Second to Sixth Month)

Formative research using qualitative methods and participatory learning and action techniques will be performed, which will help us in understanding the current practices pertaining to NCD-related risk factors and help us identify the possible opportunities and mechanisms to implement the intervention. Focus group discussions, force-field analysis, free-listing, and pile-sorting will be performed to understand the community perceptions on NCD-related risk factors, their prevention, and control. Based on the findings of the formative study, the health promotion module will be developed. These modules will be central to the participatory health promotive interventions to be implemented in the next phase. The health promotion module will have incorporated monthly session plans that will be implemented through monthly contact sessions in an incremental learning approach. The health promotion module will also emphasize deciding strategies for reaching every young person in the age group of 10-30 years and its delivery mechanisms. The strength of this strategy will be that the concerned stakeholders will be able to identify and implement initiatives that are acceptable and feasible to them (eg, stress mediation strategies, local strategies for increasing consumption of locally available and easy to access nutritious food, promotion of physical activity).

#### Phase 2: Intervention Phase (30 Months)

##### Design

The intervention phase will include the implementation of the participatory health promotion initiative based on the integrated model of communication for social change (Figure 2) [30]. Of the total duration of 30 months, 24 months will be active intervention through the study and 6 months will be the intervention without active support to assess the sustainability of the intervention. VHNSCs, although mandated to undertake preventive, promotive, and curative activities at the village level since many years, now need further capacity building to undertake such activities. The capacity of the existing VHNSCs will be used to implement the village health plan against NCDs in coordination with various community-based organizations such as SHGs, farmer groups, and adolescent groups. As discussed earlier, the health promotion module will be implemented in the community through VHNSCs, school students, and SHG members as change agents. The population in all the 4 arms will continue to receive routine care through the existing government programs for NCDs. However, no additional activities will be conducted in the control arm in this study.

**Figure 2 figure2:**
[figure not shown]
Adaptation of the integrated model of communication for social change in this study (adapted from Figueroa et al [30], which is published under Creative Commons Attribution 4.0 International License [31]). ICDS: Integrated Child Development Services; MGIMS: Mahatma Gandhi Institute of Medical Sciences; MSRLM: Maharashtra State Rural Livelihood Mission; NCD: noncommunicable disease.

##### Formation of Vitalizing Community for Health Promotion Against Modifiable Risk Factor NCD (V-CaN) Clubs

The key implementation strategies through these change agents in the intervention arms will be the formation of the Vitalizing Community for Health Promotion Against Modifiable Risk Factors of NCD (V-CaN) clubs for developing and implementing an NCD-specific health action plan for their own villages, undertaking various community-based events for health promotion, celebration of V-CaN days for spreading awareness, and creation of a social norm. The formation of these V-CaN clubs will be facilitated by the study team, and the change agents in their respective arms will be encouraged to form V-CaN clubs in their village with representation from all concerned stakeholders from that village to help disseminate and promote the learnings of the participatory health promotion module.

These V-CaN clubs will focus on preparing NCD-specific health action for themselves. The V-CaN clubs will also give emphasis on relieving stress through locally acceptable and feasible stress meditation strategies. A monthly meeting of these V-CaN clubs will be conducted to review monthly activities and ensure prompt health actions. As specified earlier, there will be no additional activities (V-CaN club formation) in the control arm; however, the population in the control arm will continue to receive routine care through the existing government program, that is, NP-NCD.

##### NCD-Specific Health Action Plan

The V-CaN club members will be expected to make a health plan against NCDs to take the learning from the monthly sessions forward. The health plan will focus on reaching every person in the age group of 10-30 years in their area. It will also include activities that they will undertake during the next 2 years for bringing about behavior change in young people. The plan will focus on identifying and implementing initiatives that are acceptable and feasible to the local community for motivating the community to indulge in pro-health behavior as described above.

##### Organizing V-CaN Days

A V-CaN day (Melawa) will be organized in all the intervention villages and schools once in every 6 months with the objective to facilitate the behavior change process in the participants to (1) give up tobacco and alcohol consumption habits, if any, (2) eat a proper balanced diet, and (3) indulge in physical activity every week. The activities on the V-CaN day will be arranged in collaboration with village level health functionaries, namely, VHNSCs, ASHA (Accredited Social Health Activist), and AWW (Anganwadi worker). The effort will be to emphasize the harmful effects of the NCD risk factors by using modes such as exhibitions, role plays, demonstrations, and participatory games. Efforts will be taken to maximize the participation in these V-CaN day celebrations.

##### Sustainability Strategy and Exit Plan

An exit plan will be prepared in consultation with the V-CaN clubs regarding how to sustain the initiative after the implementation phase of the study. Each V-CaN club will be facilitated to prepare a plan for mobilizing resources for continuing the activities of V-CaN club. In the last 6 months of the implementation phase of the study, the activities will continue without any active support from the study staff. The sustenance of activities for the next 6 months will be monitored and documented through the study and will be a proxy indicator of the sustainability of the intervention. Factors affecting sustainability will be studied through doer (villages or schools that are able to sustain) and non–doer analyses (villages or schools that are not able to sustain). We have developed a theory of change (Figure 3) and a results framework (Table 1) for the study that will be used for monitoring and evaluation (process, output, and effect) of the study and documenting the change.

**Figure 3 figure3:**
[figure not shown]
Theory of change for this study. SHG: self-help group; V-CaN: Vitalizing Community for Health Promotion Against Modifiable Risk Factors of Noncommunicable Diseases; VHNSC: Village Health Nutrition and Sanitation Committee.

**Table 1 table1:** Results framework for the proposed Vitalizing Community for Health Promotion Against Modifiable Risk Factors of Noncommunicable Diseases (V-CaN) study.

Questions	Answers	Key assumptions
What is the problem you are trying to solve?	Enabling every young person to adopt a pro-health behavior	Quality and longevity of the intervention
Who is your key audience?	All young people aged 10-30 years	Young people are receptive and value the V-CaN^a^ day messages and practice them
What is your entry point for reaching your key audience?	VHNSC^b^ members, school students, MSRLM^c^ SHG^d^ members	Health and education departments are responsive to V-CaN days and give due priority to them VHNSC members, school students, and MSRLM SHG members have interest and are committed to improving the health behavior of young people
What steps are needed to bring about the change?	Receiving administrative approvals Necessary supplies and logistics Training of trainers (supervisors) Training and capacity building of VHNSC members, school students, and MSRLM SHG members Reaching all young people aged 10-30 years through identified approaches	VHNSC members, school students, and MSRLM SHG members are able to tide over the social norms or restrictions and conduct or participate in V-CaN day activities
What is the measurable effect of your work?	Impact Obesity or overweight Prehypertension Hypertension Pro-health behavior of all young people Effect Decreased prevalence of prehypertension or hypertension Decreased prevalence of overweight or obesity Increased frequency and consumption of fruits and vegetables Increased level of physical activity Decreased stress levels Decreased tobacco use Decreased alcohol use Decreased salt intake Output V-CaN days held (number conducted or number planned) V-CaN clubs formed Proportion of young persons (10-30 years) reached	Master trainers have interest and are committed to improving the health behavior of young people Good quality in-system trainings are planned and conducted Master trainers are able to transfer the skills to VHNSC members, school students, and MSRLM SHG members
What are the wider benefits of your work?	Decreased prevalence of noncommunicable diseases	Young people have the necessary family and social support to engage in pro-health behavior
What is the long-term change you see as your goal?	A healthy and happy society	Stakeholders are young children and their parents, panchayat raj institution members, VHNSC members, school students, and MSRLM SHG members

^a^V-CaN: Vitalizing Community for Health Promotion Against Modifiable Risk Factors of Noncommunicable Diseases.

^b^VHNSC: Village Health Nutrition and Sanitation Committee.

^c^MSRLM: Maharashtra State Rural Livelihood Mission.

^d^SHG: self-help group.

##### Participatory Assessment of Change

Concurrent evaluations using the participatory method of web (spider) diagram will be performed every 6 months to assess behavior change among the young people.

#### Phase 3: Endline Assessment and Documentation (6 months)

Endline surveys and assessments for the effectiveness of health intervention measures will be performed in both the intervention and control groups. Case studies and human stories of change will be documented.

### Data Collection and Statistical Analysis Plan

#### Data Collection Tools

The data collection instrument will be designed based on the WHO-STEPwise tool for NCD risk factor surveillance during baseline as well as endline assessments [27]. The WHO-STEPwise approach to the surveillance of NCD risk factors uses a standard survey instrument and a methodology that can be adapted to different country resource settings. It will be suitably modified to meet the objectives of this study and will be pilot tested. Data will be collected on Android-based tablets by using a survey solution platform developed by the World Bank through individual surveys. Anthropometry, physical measurements, and biochemical assessments will also be conducted in young people in the age group of 10-30 years. The data collection tools will consist of (1) baseline demographic information about individuals in households (age, gender, education, occupation, socioeconomic status, etc); (2) health behaviors consisting of tobacco use in smoked and smokeless form, alcohol consumption, dietary pattern (consumption of fruits, vegetables, salt, etc), and physical activity; (3) stress measurements of the study participants by using the perceived stress scale-10 that has already been used and validated in India [32,33]; (4) physical measurements, which will include measurements of height, weight, and blood pressure; and (5) biochemical assessments, which will include fasting blood sugar and lipid profile.

Operational definitions of health behaviors and procedures for physical measurements and biochemical assessments will be as per the standard procedures in the WHO-STEPwise tool for the NCD risk factor surveillance. Height and weight will be measured as described in the WHO STEPwise surveillance module. For blood pressure measurements, all the readings will be recorded by trained personnel to reduce the interobserver variation. Training in all relevant techniques will be given, including care for avoiding expectation error and digit preference. The forearm will be kept at the level of the heart. The sphygmomanometer will also be kept at the level of the heart. Two readings of blood pressure will be taken: one at the beginning of the assessment and the second at midway in the assessment. If the first 2 readings differ by more than 5 mm Hg, an additional reading will be taken and the average of the 3 readings will be noted. For blood sugar and lipid profile, 5 mL of fasting venous blood sample will be collected and transferred to the central laboratory of the institute for further processing and reporting [34]. As specified in the methodology earlier, all the measurements would be performed on 12,000 participants, except for biochemical assessments, which will be performed for a random subset of 1600 participants from among the larger cohort of 12,000 participants. However, a separate random sampling will be performed as specified earlier for the endline assessment as well.

#### Statistical Analysis Plan

The primary outcome variable for this study would be the prevalence of various modifiable NCD risk factors as compared to baseline. Descriptive analysis will be performed using proportions with 95% CIs. For the quantitative information, difference in differences analysis using *Z*-test for differences between proportions of independent samples and ANOVA or multivariate analysis of covariance will be used to find out the effectiveness of the intervention between the intervention and the control groups. Here, the 3 interventions will be evaluated independently to demonstrate the feasibility and efficacy of each of the 3 intervention modalities. In addition, multivariate regression will be performed for finding the determinants of the risk factors, and exploratory factor analysis will be performed to explain the observed variances between intervention and control groups. For the qualitative data, thematic content analysis will be performed.

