## Methods

### Study Design

The proposed study will be a type II hybrid effectiveness implementation cluster randomized field trial that will be implemented in a rural area of Wardha district of Maharashtra, India, which also is a part of the field practice area of the Department of Community Medicine, Mahatma Gandhi Institute of Medical Sciences, India. This study will be performed in the catchment areas of 4 primary health centers (PHCs) of Wardha block, namely, Anji, Kharangana, Talegaon, and Waifad. As per the census of 2011, there are around 100 villages in this study area with a population of approximately 144,000 people. However, the census towns (as per census 2011) in the study area will be excluded [26]. This study will be performed from January 2022 to December 2024.

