### Randomization

The proposed study will have 4 arms: 3 intervention arms and 1 control arm. The unit of randomization would be PHCs and each of the 4 PHCs will be randomly allocated using a simple randomization technique through the lottery method to 1 of the 3 intervention arms or to the control arm. The primary strategy in this study would be health promotion by creating change agents. The 3 intervention arms would differ in the source of change agents. The 3 interventions in this proposed study would be with (1) school students as change agents, (2) VHNSC members as change agents, and (3) women’s SHG members as change agents.

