##### Sample Size for Behavioral Risk Factors

We hypothesize that our interventions would reduce the modifiable behavioral risk factors for NCDs by 25% over a period of 3 years. With an assumption of the lowest prevalence of NCD-related risk factors at 13% [6-8,28,29] to detect the aforesaid difference, with 95% CIs, power of 80%, intracluster correlation coefficient of 2, an approximate sample of 12,000 participants, that is, 3000 in each arm, was calculated. Sample size was estimated using the lowest risk factor prevalence, as it gives the maximum possible sample size. We will utilize stratified random sampling (stratified by gender) to select the study participants. The sampling frame will be prepared from the already existing health and demographic surveillance system, which is established by the Department of Community Medicine, Mahatma Gandhi Institute of Medical Sciences, in 5 PHCs (including the study PHCs) covering around 113 villages and a population of about 120,000 people. The health and demographic surveillance system is updated every 6-12 months, and data from the most recent round will be used for the abovementioned purpose.

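### The effectiveness test treats respondents as independent, although the trial is cluster randomized and its sample size is doubled for clustering; type I error is about 17% if that allowance carries in full into the contrast, and less if cluster effects are stable over time

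*Protocol article*

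**What the plan says.** The Study Design section of the Protocol article calls the study a "type II hybrid effectiveness implementation cluster randomized field trial". The Randomization section states: "The unit of randomization would be PHCs and each of the 4 PHCs will be randomly allocated using a simple randomization technique". With four arms, that is one PHC per arm.

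The section Sample Size for Behavioral Risk Factors takes a lowest prevalence of 13%, a 25% reduction and 80% power, and gives the clustering allowance as "intracluster correlation coefficient of 2, an approximate sample of 12,000 participants", or 3000 per arm.

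The Statistical Analysis Plan section defines the outcome: "The primary outcome variable for this study would be the prevalence of various modifiable NCD risk factors as compared to baseline". Effectiveness is to be judged by a difference in differences in which a Z "test for differences between proportions of independent samples and ANOVA or multivariate analysis of covariance will be used to find out the effectiveness". It adds: "Here, the 3 interventions will be evaluated independently to demonstrate the feasibility and efficacy of each of the 3 intervention modalities".

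No section names a cluster-level analysis, a GEE, a mixed model or a variance inflated by a design effect. The abstract mentions regression for effectiveness without saying how it would treat clusters.

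**The concern.** The sample size and the analysis rest on different assumptions. The first accepts that people in the same cluster resemble each other and pays for it with twice the respondents. The second computes its standard errors as if they did not. The intervention works through village clubs, village health plans, schools and village events, so changes between rounds are likely to be shared within villages and PHCs. A standard error that leaves this out is too small, its confidence interval too narrow, and its p-value too low. This affects each of the three comparisons with control and each risk factor, before any question of multiplicity.

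This is not a detail left to a separate analysis plan, because the article itself names the test.

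**Working it through.** **Inputs.** From Sample Size for Behavioral Risk Factors: 13% prevalence; 25% relative reduction, so 0.13 × 0.75 = 9.75%; 80% power; 5% level (from the 95% CIs; two-sided is inferred); clustering factor 2; 3000 per arm. From Randomization: one PHC per arm. From Data Collection Tools: a separate random sample at endline. Any other value below is marked as an assumption.

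**1. The plan's own figure.** For two proportions with mean 0.11375:

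n = [1.960·√(2 × 0.11375 × 0.88625) + 0.8416·√(0.13 × 0.87 + 0.0975 × 0.9025)]² / 0.0325²
= (0.8801 + 0.3774)² / 0.00105625 ≈ 1497.1, so 1498 per arm.

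Times 2 gives 2996 per arm, and times four arms 11,984, against the stated 3000 and 12,000. Other readings miss: 1498 without the factor; 3116 with a continuity correction and doubling; 2360 one-sided and doubled. An intracluster correlation cannot be 2, so the printed value works only as a design effect.

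**2. Error of the unadjusted test.** If the true variance is D times the one used, the type I error is 2·[1 − Φ(1.96/√D)]. At D = 2, 1.96/1.414 = 1.386 and the error is 16.6%. A 95% CI then covers 83.4%, and the standard error is understated by 1 − 1/√2 = 29%. At D = 1.5, 3 and 4 the error is 11.0%, 25.8% and 32.7%. A beta-binomial simulation (two PHCs, 3000 each, 13% prevalence, 400,000 replicates) gave 16.5% for an endline Z-test. It gave 16.6% for a difference in differences with cluster effects drawn afresh in each round.

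**3. What remains in a difference in differences.** Let ρ be the PHC-level ICC, m = 3000, and s the share of the cluster effect that is constant between rounds. The constant part cancels, leaving D = (1 − ρ) + mρ(1 − s). A design effect of 2 implies ρ = 1/2999 = 0.00033. Then:

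| s (assumption) | D | Type I error |
|---|---|---|
| 0% | 2.0 | 16.6% |
| 50% | 1.5 | 11.0% |
| 80% | 1.2 | 7.4% |
| 100% | 1.0 | 5.0% |

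**4. If PHC-level clustering is stronger.** The implied ρ of 0.00033 is very small. Assumed values of 0.001, 0.005 and 0.01 give 1 + 2999ρ ≈ 4, 16 and 31, and errors of 33%, 62% and 72% with nothing constant. Stability helps here too: at ρ = 0.001 with 80% constant, D = 1.6 and the error is 12%; at ρ = 0.005 with 80% constant, D ≈ 4 and the error is 33%.

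**The case against.** Four arguments on the other side carry weight.

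- **A reader might infer that the planned test simply has 17% type I error.** The documents do not support this as an unconditional figure. It needs the printed coefficient read as a design effect, which the reproduced sample size supports. It also needs the whole factor to carry into a difference in differences, which nothing in the article establishes. Stable cluster differences cancel, so the error could be near 5%.
- **A reader might go further and put the error at 29% from village clustering.** That assumes a village ICC of 0.02 and 25 villages per arm, so 3000/25 = 120 respondents per village and D = 1 + 119 × 0.02 = 3.38. The ICC is not in the article. Individuals are sampled from a surveillance frame and not by village, so only village-by-round variation counts: D = 0.98 + 2.4(1 − s). With 50%, 80% or 100% constant, D is 2.18, 1.46 or 0.98 and the error about 18%, 10% or 5%.
- **A reader might object that a Z-test cannot be a difference in differences, or that ANOVA is wrong for prevalence.** Neither holds. A Z statistic on four proportions is a legitimate contrast for repeated cross-sections. The article also has mean outcomes (the biochemical sample size and the secondary effectiveness indicators in Table 3) that ANOVA or its multivariate form can serve.
- **Independent samples may refer only to the fresh endline draw, and the abstract also mentions regression.** Both are fair readings. But a fresh draw makes the rounds independent, not the respondents within a PHC or village, and the regression is given no treatment of clusters.

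What stands is that no named method accounts for the clustering that the sample size allows for.

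**Conclusion.** The point holds: the named analysis contradicts the article's own clustering allowance, and its standard errors are too small unless cluster effects are entirely constant over time. On the plan's own factor of 2, the type I error of a nominal 5% test lies between 5% (all of the cluster effect constant) and about 17% (none constant). It is higher if the true design effect exceeds 2. These figures are per comparison and per risk factor.

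A reader might also infer that modelling villages would make the inference fully valid. The design does not allow that. With one PHC per arm, PHC-level variation cannot be separated from the intervention, and no analysis of these data can estimate it. Village-level methods correct only the understatement that arises within PHCs.

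**What to change.** For each intervention against control, replace the Z-test and ANOVA sentence with one model containing arm, round and their interaction. Use a binomial GEE or mixed model for prevalence and the linear version for continuous outcomes. Cluster on village, include a village-by-round term and a small-sample correction, and adjust for sex (the sampling stratum) and age, both already collected. A t-test on village-level changes in prevalence is a simple alternative; about 100 villages means roughly 25 per arm if they divide evenly (assumption).

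Add a statement that, with one PHC per arm, the CIs and p-values do not account for PHC-level variation, and limit the conclusions accordingly. Report a sensitivity analysis over assumed PHC-level ICCs, for example 0.0003 to 0.01, crossed with the share of the effect assumed constant. In the sample-size section, relabel the factor of 2 as a design effect if that is what was meant.

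The cost is wording, code and a little more analysis work. It needs no new data if village is carried over from the surveillance frame.

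The intervals widen, by a factor of √2 = 1.41 at a full design effect of 2. Power falls with them. For the four-proportion contrast the unadjusted standard error is √[(3 × 0.1131 + 0.0880)/3000] = 0.0119, and 0.0325/0.0119 = 2.72, which gives about 78% power. With the standard error multiplied by 1.41 it is about 49%.

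### The difference-in-differences Z-test assumes independent samples, yet both survey rounds draw on the same PHC lists and several hundred people per arm are likely to be surveyed twice; the effect is modest, conservative and secondary to ignored clustering

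*Protocol article*

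**What the plan says.** All references are to the Protocol article.

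- **Statistical Analysis Plan:** effectiveness is judged by difference in differences, using a Z-test for "differences between proportions of independent samples", with ANOVA or multivariate analysis of covariance also named. The sentence mentions neither clustering nor repeated persons.
- **Randomization:** four PHCs are allocated by lottery to four arms, so each arm is one PHC.
- **Sample Size for Behavioral Risk Factors:** the figure is 12,000, "that is, 3000 in each arm, was calculated". On where people are drawn from: "The sampling frame will be prepared from the already existing health and demographic surveillance system". That system covers 5 PHCs and about 120,000 people.
- **Abstract (Results):** the same numbers are assessed at baseline and at endline.
- **Data Collection Tools:** "a separate random sampling will be performed as specified earlier for the endline assessment as well". Nothing there excludes baseline participants from the second draw or says how someone drawn twice is linked.

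**The concern.** The draws are large relative to the lists they come from. When a sizeable share of a PHC's eligible young people is sampled at baseline, a second random draw about three years later will pick many of them again. Tobacco use, body weight and blood pressure are plausibly correlated within a person over time. The variance of a before-after change then contains a covariance term that an independent-samples Z-test omits.

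At stake are the error bars on the within-arm changes and differences in differences for the behavioral risk factors. Positive correlation makes the variance of a change smaller than the Z-test assumes, so the trial would not use precision it has already paid for. Unless records carry a common identifier at collection, the overlap may be hard to recover later.

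**Working it through.** **1. Reproduce the plan's sample size.** Inputs (Sample Size for Behavioral Risk Factors): "lowest prevalence of NCD-related risk factors at 13" percent; an aim to "reduce the modifiable behavioral risk factors for NCDs by 25% over a period of 3 years", read as relative, so 13% to 9.75%; "with 95% CIs, power of 80" percent; "intracluster correlation coefficient of 2". A value of 2 is impossible for an intracluster correlation but works as a design effect. The two-sided two-proportion formula gives 1498 per group; 1498 × 2 = 2996, which matches 3000. The factor of 2 is used below as the design effect.

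**2. Sampling fraction.** The documents do not give PHC sizes or the share aged 10-30.
- PHC population: 120,000/5 = 24,000 (surveillance frame) or 144,000/4 = 36,000 (study area), assuming PHCs of equal size.
- Share aged 10-30: assumed 35-40%.
- Fraction: 3000/(36,000 × 0.40) = 3000/14,400 = 0.208; 3000/(24,000 × 0.35) = 3000/8,400 = 0.357.
- With a share of 30-45% the range widens to 0.185-0.417.

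**3. Expected overlap.** About 3 of 21 single-year ages leave the range over three years, so 18/21 of the baseline sample stays eligible. With no migration:
- 0.208 × 18/21 = 0.179, or 536 of 3000 per arm.
- 0.357 × 18/21 = 0.306, or 918 of 3000 per arm.

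**4. Biochemical subset (400 per arm).** Fraction 400/14,400 = 0.028 to 400/8,400 = 0.048; overlap 2.4-4.1%, or about 10-16 people per arm. The standard error (SE) is wrong by 0.4-1.5%, which is negligible.

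**5. Effect of overlap alone on the SE.** With within-person correlation ρ (not in the documents; assumed 0.3-0.7) and similar variances in both rounds, the variance of a change is multiplied by (1 − overlap × ρ).

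| Overlap | ρ | Planned SE / true SE | True level of 5% test, this source only |
|---|---|---|---|
| 0.179 | 0.3 | 1.03 | 4.4% |
| 0.179 | 0.7 | 1.07 | 3.6% |
| 0.306 | 0.3 | 1.05 | 4.0% |
| 0.306 | 0.7 | 1.13 | 2.7% |

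A simulation of two separate draws of 3000 from closed lists of 14,400 and 8,400, without clustering and with ρ of 0.3 and 0.5, gave true/planned SE ratios of 0.915-0.977 and null rejection of 3.2-4.6%. Direction and order of size agree.

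**6. Add clustering.** The Z-test's SE for the difference in differences is √[(3 × 0.1131 + 0.0880)/3000] = 0.0119. At design effect 2 it should be 0.0119 × √2 = 0.0169. Without overlap, the unadjusted test's true level is 2 × [1 − Φ(1.96/√2)] = 16.6%.

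With overlap, the person-level covariance is not inflated by the design effect, so true variance / planned variance = 2 − overlap × ρ:
- 2 − 0.054 = 1.946, level 16.0%.
- 2 − 0.214 = 1.786, level 14.2%.

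If the whole inflated variance is instead multiplied by (1 − overlap × ρ), the level is 15.4% to 11.8%. Either way it lies at about 12-17%, well above 5%.

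**7. Power at design effect 2 for a difference of 0.0325.**
- Overlap ignored: Φ(0.0325/0.0169 − 1.96) = 49%.
- Overlap modelled: SE = 0.0119 × √1.946 = 0.01665, power 50%; SE = 0.0119 × √1.786 = 0.01595, power 53%.
- The gain is about 1-4 points. Figures of 51-58% appear only if the design effect is also applied to the person-level covariance.

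**The case against.** **The error is in the safe direction and repeated cross-sections are ordinary.** Taken alone, overlap with positive correlation cannot create a false positive, and linking people drawn twice is often left to a statistical analysis plan. This limits the weight of the point but does not remove it, because the article itself names the test and its independence assumption.

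**The upper figures rest on inputs outside the documents.** This stands. The age share, equal PHC sizes, full response and ρ are assumptions, and 21-36% is not a document figure. No migration is a worst case for overlap, since Table 2 lists migration as an external factor. In the other direction, excluding census towns and people with severe or chronic illness shrinks the eligible pool by unstated amounts.

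**Independent draws have no design covariance.** For a fixed finite population, two separate draws give uncorrelated estimates despite shared members. The planned SE is still too large on that view, because the finite-population correction is ignored. Independence between arms is not in dispute as regards overlap: the arms contain different people.

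**A stronger reading.** A reader might infer that every SE in the trial is overstated and that the test's true level is 2.7-4.4%. The documents do not support that. Those levels hold only without clustering, while the plan's own sample size carries a factor of 2. On that basis the net SE is too small, and the biochemical outcomes are hardly touched by overlap.

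**Conclusion.** The assumption of independence between rounds does not fit the sampling plan. Roughly 540-920 of 3000 people per arm would appear in both behavioral samples, given 24,000-36,000 people per PHC, 35-40% aged 10-30, 18 of 21 age years retained and no migration. With ρ of 0.3-0.7, that source alone makes the SE 3-13% too large and costs about 1-4 points of power.

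This is a secondary point. Ignored clustering in the same test is larger and opposite in sign, so the net result is anti-conservative. Correcting the overlap without the clustering would shrink an SE that is already too small.

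**What to change.** - State whether baseline participants may be selected again at endline.
- Carry one person identifier into both rounds and report the number of people in both, by arm. The Ethics Approval section already assigns each participant a unique number; it must be the same number in both rounds.
- Replace the Z-test with a regression of each risk factor on arm, round and arm-by-round, with a variance that allows for both village clustering and repeated persons. Options are random effects for village, village-by-round and person, or robust variance clustered on village, which also covers repeated persons who stay in their village.
- State that this does not remove the confounding of arm with PHC: with one PHC per arm, no model can separate the intervention from a PHC-specific trend.

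The cost is keeping a linkage key and adding variance terms to the model; no extra participants are needed. The small downside is that the key must be held securely under the existing confidentiality rules.
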